**Methods:**

This type-2 hybrid implementation-effectiveness study includes formative work, qualitative assessments, and clinical steps 1 to 4. For formative work, we will use participatory design methods to develop an initial CAB-LA implementation package and process mapping at each site to facilitate optimal client flow. SGMs aged 18 to 30 years arriving at a study clinic interested in PrEP (naive) will be invited for step 1. Individuals who tested HIV negative will receive mHealth intervention and standard of care (SOC) counseling or SOC for PrEP choice (oral or CAB-LA). Participants interested in CAB-LA will be invited for step 2, and those with undetectable HIV viral load will receive same-day CAB-LA injection and will be randomized to receive digital appointment reminders or SOC. Clinical appointments and CAB-LA injection are scheduled after 1 month and every 2 months thereafter (25-month follow-up). Participants will be invited to a 1-year follow-up to step 3 if they decide to change to oral PrEP or discontinue CAB-LA and to step 4 if diagnosed with HIV during the study. Outcomes of interest include PrEP acceptability, choice, effectiveness, implementation, and feasibility. HIV incidence in the CAB-LA cohort (n=1200) will be compared with that in a similar oral PrEP cohort from the public health system. The effectiveness of the mHealth and digital interventions will be assessed using interrupted time series analysis and logistic mixed models, respectively.

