**Results:**

During the third and fourth quarters of 2022, we obtained regulatory approvals; programmed data entry and management systems; trained sites; and performed community consultancy and formative work. Study enrollment is programmed for the second quarter of 2023.

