##### Specific Visit Procedures

Participants included in step 2 to receive CAB-LA PrEP who decide to discontinue participation before completing the minimum 1 year and maximum 2 years of study follow-up will complete early discontinuation visit procedures (Table 3). These participants will be invited to participate in a 12-month extension follow-up to safely monitor the CAB-LA “tail” phase and will be offered oral PrEP (TDF and FTC). Some of them will be invited to participate in a qualitative interview to describe their experience with CAB-LA PrEP and the reason for decision to discontinue CAB-LA PrEP.

If a participant misses an appointment but wishes to continue with CAB-LA PrEP, reloading with CAB-LA may be necessary, and the participant will need repeat HIV rapid tests before receiving a new CAB-LA injection. Oral bridging with TDF and FTC will be offered to participants who anticipate not being able to attend their scheduled injections (planned missed injections) in the +7 or −7-day window, starting approximately 2 months after the last injection dose of CAB-LA.

**Table 3 table3:** The ImPrEP CAB Brasil–specific visit procedures.

Procedures			Final visit		Early discontinuation^a^		Seroconversion		STI^b^ interim visit		AE^c^ interim visit

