### Statistical Analysis

Our major clinical outcome (primary analysis) will adopt an intent-to-treat approach and compare HIV incidence (and 95% CI) among individuals in the CAB-LA cohort with HIV incidence (and 95% CI) among individuals on daily PrEP within the Brazilian SUS. We will estimate the rate of HIV incidence with 95% CI in each group using Kaplan-Maier statistics. We will use a Cox proportional hazard model to assess the relative hazard (hazard ratio with 95% CI) between the 2 groups, overall and by site, age category, and gender.

It is anticipated that there will be an average follow-up of 1.5 years per person with at least 75% retention each year (N=1350 person-years of follow-up) and that incidence will be higher than that observed in HPTN 083 in Latin America (0.60 per 100 person-years). If the observed incidence is approximately 50% higher than that observed in HPTN 083, the study will be able to estimate an incidence of 0.85 (95% CI of 0.47-1.42) per 100 person-years (Table 6). If the observed incidence is approximately twice as high as that observed in HPTN 083, then the study will be able to estimate an incidence of 1.18 (95% CI of 0.72-1.82) per 100 person-years. If the comparison group is of similar size, then the incidence would need to be 2.2 to 2.5 times higher to observe statistically significant differences between CAB-LA and oral PrEP. However, if the comparison group is 3 times larger, then the incidence would need to be 2 to 2.2 times higher to observe statistically significant differences between CAB-LA and oral PrEP.

To reach the primary implementation objective, we will report descriptive statistics (numbers, proportions, and medians) of Likert-scale responses to the TFA constructs (affective attitude, burden, ethicality, intervention coherence, opportunity costs, and perceived effectiveness and self-efficacy) among health care providers.

**Table 6 table6:** Observable differences given potential HIV incidence in intervention and comparison groups.

Group				Incidence (95% CI)

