## Results

During the third and fourth quarters of 2022, we obtained regulatory approvals; programmed data entry or management systems; trained sites; and performed community consultancy, process mapping, and formative work. Study enrollment is anticipated to happen in the first quarter of 2023. The planned activities are presented in Table 7.

**Table 7 table7:** Planned activities for the ImPrEP CAB Brasil study (2022-2024).

Activities	Quarter 2 of 2022	Quarter 3 of 2022	Quarter 4 of 2022	Quarter 1 of 2023	Quarter 2 of 2023	Quarter 3 of 2023	Quarter 4 of 2023	Quarter 1 of 2024	Quarter 2 of 2024	Quarter 3 of 2024	Quarter 4 of 2024
Regulatory submission	✓										
Regulatory approvals		✓	✓								
Data entry or management systems programmed	✓	✓									
Drug importation and distribution				✓	✓						
Site equipping	✓	✓	✓								
SOP^a^ and SSP^b^ development	✓	✓	✓	✓							
Staff selection	✓	✓									
Staff training		✓	✓								
Process mapping			✓								
Formative work		✓	✓	✓							
Enrollment					✓	✓	✓				
Follow-up						✓	✓	✓	✓	✓	
Data consolidation							✓	✓	✓	✓	
Data analysis										✓	✓
Final report											✓
Manuscript submission											✓

^a^SOP: standard operational procedures.

^b^SSP: study-specific plan.

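### The Table 7 calendar allows 9 to 18 months of follow-up per person, which contradicts the 1-to-2-year range, the 25-month schedule and the 1.5-year mean behind the 1350 person-years

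*Protocol article*

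**What the plan says.** The Statistical Analysis section states: "It is anticipated that there will be an average follow-up of 1.5 years per person with at least 75% retention each year". It puts the total at "N=1350 person-years of follow-up". The abstract gives the cohort size: "HIV incidence in the CAB-LA cohort (n=1200) will be compared with that in a similar oral PrEP cohort from the public health system".

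Three places describe how long a participant is followed in step 2:
- The abstract's Methods: "Clinical appointments and CAB-LA injection are scheduled after 1 month and every 2 months thereafter (25-month follow-up".
- Table 2, which lists visits and injections from month 15 to month 25.
- Specific Visit Procedures, which speaks of stopping "before completing the minimum 1 year and maximum 2 years of study follow-up".

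The calendar is Table 7 in the Results section, titled "Planned activities for the ImPrEP CAB Brasil study (2022-2024". It ticks:
- enrollment in Q2, Q3 and Q4 of 2023;
- follow-up from Q3 of 2023 to Q3 of 2024;
- data analysis in Q3 and Q4 of 2024;
- the final report in Q4 of 2024.

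The abstract's Results agree on the start: "Study enrollment is programmed for the second quarter of 2023". The running text above Table 7 instead expects enrollment in the first quarter of 2023.

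**The concern.** The article prints two follow-up plans that do not fit together. One is the follow-up period used for visits and for the person-year calculation. The other is the calendar, which closes follow-up before that period can be completed.

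Person-years set the precision of the primary clinical outcome. The 1350 figure is the base of the CAB-LA rows of Table 6 and of the stated detectable ratios (2.2 to 2.5 with a comparator of similar size, 2 to 2.2 with one three times larger). If the 1.5-year mean is not supported by the calendar, those figures rest on an input that the document itself contradicts.

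The one-year follow-up in steps 3 and 4 is also exposed. Anyone who enters either step after the end of Q3 2023 cannot complete 12 months by the end of Q3 2024.

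**Working it through.** **1. Reproduce the plan's figure.** Inputs: 1200 participants (abstract), a 1.5-year mean and 75% retention (Statistical Analysis).

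1200 × 1.5 × 0.75 = 1350. This matches exactly, so the product contains no arithmetic slip. The question is whether the 1.5 is available.

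**2. Limits set by Table 7.** Time is counted from enrollment, which is the generous reading, because the follow-up ticks begin only in Q3 of 2023.

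- Longest: 1 April 2023 to 30 September 2024 = 18 months.
- Shortest: 31 December 2023 to 30 September 2024 = 9 months.

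These limits need no accrual assumption. A 1.5-year mean would require all 1200 to enroll on the first day of Q2 2023. Anyone enrolled after 30 September 2023 falls short of 1 year. On this calendar nobody reaches months 19 to 25.

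**3. Does the Q1 2023 start repair it?** From 1 January 2023 to 30 September 2024 is 21 months. Months 23 and 25 and the 2-year maximum remain out of reach, and the minimum is still 9 months. With even accrual over Q1 to Q4 the mean is (9 + 21)/2 = 15 months, or 1.25 years.

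**4. Expected person-years at 75% retention per year.** The documents do not state the accrual pattern, so a range is shown. Two loss models are used:
- Plan's formula: 1200 × mean follow-up × 0.75.
- Gradual loss: 1200 × the average of (1 − 0.75^t)/(−ln 0.75) over scheduled follow-up t.

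| Enrollment, follow-up to end of Q3 2024 | Mean (years) | Plan's formula | Gradual loss | No loss |
|---|---|---|---|---|
| Even over Q2-Q4 2023 (Table 7) | 1.125 | 1012.5 | 1147 | 1350 |
| Even over Q1-Q4 2023 (Results text) | 1.25 | 1125 | 1250 | 1500 |
| All within Q2-Q3 2023 | 1.25 | 1125 | 1257 | 1500 |
| All within Q2 2023 | 1.375 | 1237.5 | 1362 | 1650 |

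For the first row, the shortfall against 1350 is 1 − 1012.5/1350 = 25% by the plan's formula and 1 − 1147/1350 = 15% with gradual loss. Under even accrual, one third of participants (those enrolled in Q4) cannot reach 1 year.

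**5. Precision.** The middle CAB-LA row of Table 6 has 12 cases in 1350 person-years. A mid-P Poisson interval gives 0.89 (0.48-1.51), which reproduces the printed row. At the same rate:
- 12/1350 × 1012.5 = 9.0 expected cases;
- 12/1350 × 1147 = 10.2 expected cases.

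The mid-P interval for 9 cases in 1012.5 person-years is 0.89 (0.43-1.63).

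**6. Detectable ratio.** The check takes the smallest comparator count that is significant by a conditional mid-P test.
- Comparator of equal size: 24 against 12 cases at 1350 person-years each (ratio 2.0), and 20 against 9 at 1012.5 each (ratio 2.2).
- Comparator three times larger: the ratio moves from 1.8 to 1.96.

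**The case against.** **1350 is not ruled out.** A reader might infer that 1350 person-years cannot be delivered. The documents do not support that. The plan states 75% as a floor. Table 7 yields exactly 1350 under even accrual with no loss, and 1350 also follows from a 1.25-year mean with 90% retention (1200 × 1.25 × 0.90). Enrolling everyone within Q2 2023 gives 1362 with gradual loss. This objection stands, and it limits the claim to what is expected under even accrual at 75% retention.

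**The calendar may be coarse or out of date.** If follow-up ran through Q4 2024, the Table 7 start would give 12 to 21 months and a mean of 1.375 years: 1237.5 person-years by the plan's formula and 1357 with gradual loss. If enrollment also began in Q1 2023, the range would be exactly 1 to 2 years with a mean of 1.5, and the plan's formula would return 1350. That suggests the Statistical Analysis section was written for such a calendar, but it does not prove it. The article nowhere shows that calendar, and Table 7 and the abstract both place the start in Q2.

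**The effect is modest.** This also stands. The interval widens only a little, and the recalculated ratios for the middle row (2.2 and 1.96) are no worse than the ratios the plan already quotes.

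**Steps 3 and 4.** A reader might infer that most people entering these steps would be cut short. The article gives no distribution of entry times, so that share cannot be stated.

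None of these points restores the 1.5-year mean, the 1-year minimum or month 25 under Table 7.

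**Conclusion.** The inconsistency is real. Table 7 permits 9 to 18 months per person, against a stated range of 1 to 2 years, a schedule running to month 25 and a mean of 1.5 years. This does not depend on how participants accrue or how many are retained. The Q1 2023 start in the Results text conflicts with Table 7 and the abstract and does not resolve it.

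The size of the person-year shortfall does rest on assumptions. With even accrual and 75% retention per year, about 1010 to 1150 person-years are expected, 15% to 25% below 1350. Earlier-loaded accrual narrows or closes the gap: 1125 to 1257 if all enroll in Q2-Q3 2023, and 1238 to 1362 if all enroll in Q2 2023. So 1350 is not the expected figure under even accrual at the planning retention, though it is not impossible. The consequence for precision is moderate, and the correction is inexpensive.

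**What to change.** Reconcile the calendar with the follow-up passages, and state one enrollment start throughout. There are two ways to do it.

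- **Keep Table 7.** Restate mean follow-up (about 1.1 years under even accrual) and person-years (about 1010 to 1150, with the accrual and loss assumptions named). Regenerate the CAB-LA rows of Table 6 and the detectable ratios. The cost is a recalculation and slightly less favourable precision.
- **Extend Table 7.** Move the follow-up, analysis and report dates until they support the stated mean and the 1-to-2-year range. With even accrual over Q2 to Q4 2023, a cut in mid-February 2025 gives 13.5 to 22.5 months and a mean of 1.5 years. The cost is a later final report, with no extra participants. This date still does not reach month 25: the earliest enrollee gets there on 1 May 2025 and the latest at the end of January 2026.

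Under either option, the sponsor should also reconcile the month-25 visit and injection schedule, and the 12-month follow-up of steps 3 and 4, with the calendar that is kept. No change to that schedule is proposed here.

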**Intervention: CAB-LA^a^ **PrEP**^b^**				
	**1350 py^c^ incidence/100 py**			
		8 cases	0.59 (0.28-1.13)	
		12 cases	0.89 (0.48-1.51)	
		18 cases	1.19 (0.71-1.88)	

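### The precision quoted in the text matches about 1530 person-years, not the stated 1350, and Table 6's 18-case row does not give its printed rate

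*Protocol article*

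**What the plan says.** In the protocol article, the abstract gives a CAB-LA cohort of 1200. The Statistical Analysis section assumes an "average follow-up of 1.5 years per person with at least 75% retention each year (N=1350 person-years of follow-up"). It expects that "incidence will be higher than that observed in HPTN 083 in Latin America (0.60 per 100 person-years") and describes two scenarios:

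- About 50% higher than that reference: "the study will be able to estimate an incidence of 0.85 (95% CI of 0.47-1.42) per 100 person-years (Table 6").
- About twice as high: the study would "estimate an incidence of 1.18 (95% CI of 0.72-1.82) per 100 person-years".

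Table 6 covers the CAB-LA cohort under a 1350 person-year heading, with three rows:

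- 8 cases, 0.59 (0.28-1.13)
- 12 cases, 0.89 (0.48-1.51)
- 18 cases, printed as "1.19 (0.71-1.88")

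The same section says the comparator incidence would have to be 2.2 to 2.5 times higher with a comparison group of similar size, and 2 to 2.2 times higher with one three times as large.

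**The concern.** The text cites Table 6 for figures that the table does not contain. Both are supposed to describe the same cohort at the same person-time, so at least one is wrong. The table's third row also fails simple division: 18 events over 1350 person-years is not 1.19 per 100.

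These sentences and Table 6 are where the article states the precision of its primary clinical outcome. As printed, a reader cannot tell whether 75% or 85% retention was planned for, or whether the upper scenario means 16 or 18 infections. The error runs in the favourable direction, because the text promises tighter intervals than the stated person-time supports.

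**Working it through.** **Inputs.** Cohort 1200 (abstract). Mean follow-up 1.5 years, retention 75%, 1350 person-years and reference rate 0.60 per 100 (Statistical Analysis). Case counts, rates and limits from Table 6. The article does not name its interval method, so it has to be identified from the table.

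**Person-years.** 1200 × 1.5 × 0.75 = 1350. The stated figure reproduces.

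**Interval method.** Rate = 100 × cases / person-years. For x cases, the mid-P Poisson limits on the expected count m solve:

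- lower: P(X > x | m) + ½P(X = x | m) = 0.025
- upper: P(X < x | m) + ½P(X = x | m) = 0.025

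Each is then multiplied by 100 / person-years. At 1350 person-years this gives 0.593 (0.275-1.125) for 8 cases and 0.889 (0.482-1.511) for 12, as printed. The nine comparator rows also reproduce to within 0.01, so mid-P is taken as the table's method.

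**Text figures at 1350 person-years.**

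- 0.85 would need 0.0085 × 1350 = 11.5 cases. Eleven cases give 0.81 (0.43-1.42) and twelve give 0.89 (0.48-1.51), so no whole count gives 0.85.
- 1.18 would need 0.0118 × 1350 = 15.9 cases. Sixteen give 1.185 (0.70-1.88), not 0.72-1.82.
- Exact Poisson, Byar, log-normal, Wald, Clopper-Pearson and Wilson limits do not return either text interval at 1350 person-years.

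**Where the text figures come from.** A search over whole case counts and person-years from 1200 to 1800 finds one mid-P solution for both text estimates: 1529 to 1531 person-years. Exact Poisson finds none.

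| Cases / person-years | Rate (mid-P 95% CI) | Text |
|---|---|---|
| 13 / 1530 | 0.850 (0.473-1.416) | 0.85 (0.47-1.42) |
| 18 / 1530 | 1.176 (0.719-1.823) | 1.18 (0.72-1.82) |

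All six text figures match, and 1200 × 1.5 × 0.85 = 1530.

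**Table 6, third CAB-LA row.** 18/1350 = 1.333 (0.815-2.066), against the printed 1.19 (0.71-1.88). 16/1350 = 1.185 (0.702-1.884), which fits apart from 0.01 on the lower limit. Three other features of the article point to 16:

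- *Scenario.* 1.19/0.60 = 1.98, about twice the reference. 1.33/0.60 = 2.2.
- *Comparator rows.* The counts look chosen so that their lower limit just clears the CAB-LA upper limit. Against 1.51 (12 cases) the printed lower limits are 1.53, 1.52 and 1.53. Against 1.88, the rows with 36, 66 and 94 cases have 1.90, 1.91 and 1.89. None of those clears 2.07, the upper limit for 18 cases.
- *Detectable ratios.* At equal size, 30/12 = 2.50 and 36/16 = 2.25. At three times the size, 78/(3 × 12) = 2.17 and 94/(3 × 16) = 1.96. These are the stated 2.2-2.5 and 2-2.2. With 18 cases, 36/18 = 2.00 and 94/(3 × 18) = 1.74, which contradict the text.

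**Size.** Interval widths, text against 1350 person-years:

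- 1.42 − 0.47 = 0.95 against 1.51 − 0.48 = 1.03 (8% narrower)
- 1.82 − 0.72 = 1.10 against 1.88 − 0.70 = 1.18 (7% narrower)

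The label 18 exceeds 16 by 2 (12.5%). If 18 were intended, the rate would be 1.33, 12% above the printed 1.19.

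**The case against.** The strongest reply is that these are editorial slips with little reach. The other Table 6 rows are right, the detectable ratios follow from 1350 person-years with 12 and 16 cases, and enrolment is fixed at 200 per site regardless. A reader who follows the citation to Table 6 finds sound intervals there, apart from the label on one row. The 7-8% also mixes two effects in the first scenario, where the rate moves from 0.85 to 0.89. At a fixed rate the widening is about √(1530/1350) = 1.06, or 6%. Finally, 85% retention and 1530 person-years appear nowhere in the article, and the retention assumption is worded as a minimum.

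Much of this stands. The size is modest, most of the table is correct, and the 85% is an inference. Taken alone, single figures can fit other pairs: 1.18 (0.72-1.82) fits 20 cases in about 1693-1701 person-years, and 1.19 (0.71-1.88) fits 18 cases in about 1510-1513, both by exact Poisson. None of these is at 1350, however, so none rescues the printed figures. Reading 75% as a floor does not help either, because the text puts the person-years at 1350 and cites a table built on that number. That the ratios rest on 1350 shows that two person-time bases are mixed in one paragraph.

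**Conclusion.** The concern holds. Two points need no assumption: the text cites Table 6 for an estimate that the table does not contain, and 18/1350 is not 1.19 per 100. That no whole count at 1350 person-years gives 0.85 is also plain arithmetic.

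Two further points are strong inferences. The text figures rest on about 1530 person-years (85% retention), given mid-P limits. The third CAB-LA row was meant to read 16 cases. The sponsor should confirm both.

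The consequence is limited to stated precision: text intervals 7-8% too narrow for the stated person-time, and one event count 12.5% too high. The 8- and 12-case rows, the comparator rows and the detectable ratios are not affected. It still has to be corrected, because these are wrong printed figures for the primary clinical outcome.

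**What to change.** Put the text, Table 6 and the retention assumption on one person-time basis.

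- **Keeping 75% retention and 1350 person-years:** replace the text estimates with 0.89 (0.48-1.51) for 12 cases and 1.19 (0.70-1.88) for 16 cases. In Table 6, change the third CAB-LA count from 18 to 16 and its lower limit from 0.71 to 0.70. The detectable ratios can stay.
- **If 85% was intended:** state 85% and 1530 person-years, rebuild all of Table 6 on that basis, and recheck the detectable ratios.

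In either case, name the interval method. If the person-years assumption changes for another reason, regenerate text and table together.

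The first option costs only wording in the text and table, and the stated precision becomes slightly less favourable. The second also requires recalculating the table.

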Owing to user adherence challenges, PrEP has not decreased HIV incidence among some population, particularly among populations with higher susceptibility (youth, racial and ethnic minorities, and TGW) [17-20]. Although HIV incidence in the ImPrEP study population was relatively low (0.85/100 person-years), it was higher among TGW, participants from Peru, those aged 18 to 30 years, Black or mixed-race participants, and those who were nonadherent to daily oral PrEP [15,16]. These disproportionately worse outcomes reinforce the potential of PrEP agents that do not require daily or planned oral dosing to increase their effective use among the most susceptible populations.

In multiple studies, reasons for discontinuing or never initiating daily oral PrEP include low HIV perceived risk, concerns about medication side effects, desire not to take a daily pill, stigma, competing life events, and challenges accessing the medication [13,21-23]. Long-acting PrEP agents may potentially address some of these concerns by providing consistent protection through infrequent, discrete administration, avoiding the need for daily adherence to an oral regimen and the related need for disclosure to sex partners and acquaintances [24].

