**Comparison: oral PrEP in the Brazilian health system**				
	**1350 py^c^ incidence/100 py**			
		24 cases	1.78 (1.17-2.61)	
		30 cases	2.22 (1.53-3.13)	
		36 cases	2.67 (1.90-3.65)	

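### The incidence ratios given as needed for statistical significance are points where two separate 95% CIs stop overlapping, so the significance threshold for the primary clinical comparison is overstated

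*Protocol article*

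**What the plan says.** The Statistical Analysis section of the protocol article plans two things for HIV incidence. Each group gets its own estimate: "We will estimate the rate of HIV incidence with 95% CI in each group using Kaplan-Maier statistics". The groups are then compared by a model: "We will use a Cox proportional hazard model to assess the relative hazard (hazard ratio with 95% CI) between the 2 groups".

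The section goes on to say what the study could show. CAB-LA follow-up is put at 1350 person-years (py). With a comparator of similar size, "the incidence would need to be 2.2 to 2.5 times higher to observe statistically significant differences between CAB-LA and oral PrEP". Further, "if the comparison group is 3 times larger, then the incidence would need to be 2 to 2.2 times higher". Neither sentence names a test, a significance level or a power.

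The support offered is Table 6. It lists case counts, rates and a separate 95% CI for each group, with comparators of 1350, 2700 and 4050 py. It contains no ratio, no CI for a ratio and no p-value.

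**The concern.** Both sentences are worded as a threshold for statistical significance. If the threshold came from the planned comparison, the 95% CI of the rate ratio at those values should only just exclude 1. In Table 6, however, the comparator's lower limit sits just above the CAB-LA upper limit in row after row. That suggests the ratios were found by pushing the comparator count up until the two intervals separated.

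Non-overlap of two 95% CIs is a much stricter condition than a 5% test of the difference. A reader who takes the sentences at face value would expect a larger observed difference to be needed than the planned analysis requires. The reader would also not learn what true difference the study has a good chance of detecting.

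**Working it through.** **Inputs.** All are from Table 6 and the Statistical Analysis section: CAB-LA 8, 12 and 18 cases in 1350 py; comparator 24/30/36 in 1350 py, 43/54/66 in 2700 py and 60/78/94 in 4050 py; planned comparison a hazard ratio with 95% CI, taken here as two-sided 5%. With constant hazards the rate ratio stands in for the hazard ratio.

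**Step 0: the third CAB-LA row.** The table prints 18 cases with 1.19 (0.71-1.88). 18/1350 is 1.33 per 100 py, with mid-P Poisson CI 0.82-2.07. 16/1350 is 1.19, with CI 0.70-1.88. I therefore use 16. The stated ratios also require it: 36/16 = 2.25 and (94/3)/16 = 1.96, whereas 18 cases would give 2.00 and 1.74.

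**Step 1: reproduce the stated ratios.** Mid-P Poisson limits reproduce the Table 6 intervals to within 0.01. For each CAB-LA count, I looked for the smallest comparator count whose lower limit exceeds the CAB-LA upper limit.

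| Comparator | Smallest non-overlapping count (8 / 12 / 16 CAB-LA cases) | Table 6 |
|---|---|---|
| 1350 py | 24 / 30 / 36 | 24 / 30 / 36 |
| 2700 py | 42 / 54 / 66 | 43 / 54 / 66 |
| 4050 py | 60 / 78 / 94 | 60 / 78 / 94 |

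Eight of nine match exactly, and the ninth differs by one. The 12- and 16-case rows give

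- similar size: 30/12 = 2.50 and 36/16 = 2.25;
- three times larger: (78/3)/12 = 2.17 and (94/3)/16 = 1.96.

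These are the stated ranges of 2.2-2.5 and 2-2.2.

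**Step 2: the two-group comparison at those pairs.** With a CAB-LA cases, b comparator cases and k the ratio of person-years, RR = (b/k)/a, SE(ln RR) = √(1/a + 1/b) and z = ln RR / SE. For 12 vs 30: ln 2.50 = 0.916, SE = √(1/12 + 1/30) = 0.342, z = 2.68.

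| Pair (k) | RR (95% CI, Wald) | p: Wald | p: exact | p: mid-P |
|---|---|---|---|---|
| 12 vs 30 (1) | 2.50 (1.28-4.88) | 0.007 | 0.008 | 0.005 |
| 16 vs 36 (1) | 2.25 (1.25-4.05) | 0.007 | 0.008 | 0.006 |
| 12 vs 78 (3) | 2.17 (1.18-3.98) | 0.013 | 0.010 | 0.007 |
| 16 vs 94 (3) | 1.96 (1.15-3.33) | 0.013 | 0.011 | 0.008 |

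This is what non-overlap implies. On the log scale, with s = 1/√cases, it requires z of about 1.96 (s₁ + s₂)/√(s₁² + s₂²). For 12 vs 30 that is 1.96 × 0.471/0.342 = 2.70, where a 5% test requires 1.96.

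**Step 3: smallest observed ratio with two-sided p < 0.05.**

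| CAB-LA cases (k) | Mid-P | Wald | Exact |
|---|---|---|---|
| 12 (1) | 24, RR 2.00 | 24, RR 2.00 | 25, RR 2.08 |
| 16 (1) | 30, RR 1.88 | 30, RR 1.88 | 31, RR 1.94 |
| 12 (3) | 65, RR 1.81 | 67, RR 1.86 | 68, RR 1.89 |
| 16 (3) | 81, RR 1.69 | 83, RR 1.73 | 83, RR 1.73 |

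The threshold is therefore about 1.9-2.1 for similar size and 1.7-1.9 for three times larger.

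**Step 4: what the stated ratios do describe.** Treat the four pairs as expected counts, enumerate over two Poisson counts and apply a 5% test. Power is 0.78-0.81 with mid-P and 0.76-0.81 with a score test. The true ratios giving 80% power by the score test are 2.48 and 2.24 (similar size) and 2.20 and 2.01 (three times larger).

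**The case against.** The best defence is that these are planning sentences. The section already commits to a hazard ratio with 95% CI, Table 6 presents itself as a display of observable differences, and the printed ratios are sound as differences detectable with about 80% power. The error is also conservative. All of that stands, and it limits the point to a correction of wording. It does not rescue the sentences: they speak of what is needed to observe significance, they state no power, and for an observed ratio the figures are too high.

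The non-overlap origin is inferred, since the article does not name it. Eight exact matches out of nine make another origin unlikely, and Steps 2 and 3 hold whatever the origin.

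Three stronger readings are tempting, but the document does not support them.

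- A reader might infer that results will be judged by CI overlap. The plan contains no such rule; the comparison is by hazard ratio.
- A reader might infer that the 8-case row, with ratios of 3.0 and 2.5, was left out of the text to flatter the study. The row is printed in Table 6, and the text expects incidence above the HPTN 083 rate of 0.60 and discusses only the two higher scenarios.
- A reader might set the comparator rates against the Background statement that "HIV incidence in the ImPrEP study population was relatively low (0.85/100 person-years" and call them unrealistic. Those rates are back-solved thresholds, not forecasts. The 0.85 comes from a three-country study not restricted to ages 18 to 30, and the same sentence says incidence was higher in that age group.

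**Conclusion.** The point holds as a misstated significance threshold for the primary clinical comparison. The printed ratios exceed the observed ratio needed for p < 0.05 by about 0.2 to 0.5: 2.50 against 2.0-2.1, 2.25 against about 1.9, 2.17 against 1.8-1.9, and 1.96 against about 1.7. The planned Cox analysis is unaffected, and no sample size follows from the error.

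The figures assume a two-sided 5% level, constant hazards, no covariate adjustment, no allowance for clustering by site, and 16 cases in the third CAB-LA row. The thresholds are ranges over mid-P, Wald and exact tests. No single value should be printed as exact, because the tests differ by up to three events. Adjustment for differences between the cohorts could move the thresholds.

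**What to change.** Replace the two sentences in the Statistical Analysis section with wording such as: *An observed incidence ratio of about 1.9-2.1 (comparator of similar size) or 1.7-1.9 (three times larger) would be statistically significant at the two-sided 5% level; true ratios of about 2.2-2.5 or 2.0-2.2, respectively, would be detected with about 80% power.* State the assumptions beside it: 12 to 16 CAB-LA cases in 1350 person-years, constant hazards and no covariate adjustment.

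In Table 6, correct the 18-case label so that it agrees with the printed rate and CI; 16 cases fits.

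The cost is two sentences and one table entry. Design, sample size and analysis stay as they are.
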